### Conditions

#### Experimental Condition

The i♥rhythm project comprises five 15-minute sessions focused on (1) having consistent daily bedtimes; (2) providing opportunities for sunlight exposure during the day and minimizing exposure to artificial light at night; (3) providing opportunities for activity during the day so that the child is ready to fall asleep at night; (4) ensuring the last bite of food is 1-2 hours before bed; and (5) reviewing and developing of a maintenance plan.

Self-determination theory was used to guide adaptation of the behavior change components of the intervention [42]. Self-determination theory aims to promote sustained behavior change by emphasizing intrinsic motivation, in this case promoting the satisfaction of 3 basic psychological needs: autonomy (independence to choose to change behavior), competence (belief in one’s ability to perform a behavior), and relatedness (alignment with one’s core beliefs and values) [42].

The 5-week session intervention framework and flow are presented in Figure 2. The first 4 sessions will each involve a series of videos and multiple-choice questions that guide parents through the following: (1) identification of a value that is important to them as a parent, such as having a healthy child, being spiritual, being a role model, being responsible; (2) identification of a reason why they might want to encourage their child to have a regular bedtime that is consistent with the value they selected; (3) education regarding the topic of the week and relevance to promoting a consistent bedtime; (4) implementation intention in which parents set their intention for their child’s bedtime that week and make an action plan for how they would achieve that bedtime goal utilizing skills that were introduced in the educational video; (5) identification of potential barriers to achieving their action plan; and (6) development of a coping plan in the event they encounter the identified barriers. The final screen will contain a summary of their responses, links to additional resources, and an option to print the plan (Multimedia Appendix 1). In between sessions parents will monitor and record their child’s bedtime. Daily light exposure, physical activity, and whether the child’s last bite of food was 1-2 hours before bedtime will be monitored on an intermittent basis beginning the week the topic is introduced. The fifth session will review the 4 topics and guide families through the development of a maintenance plan using open-ended questions. A summary of the developed maintenance plan is provided to participants at the end of the session. The sessions have been developed and programmed on an online survey platform called Alchemer [43].

Considering the developmental abilities of children aged 5-8, parents are considered the primary agent of change, though child viewing of the videos is encouraged. Session links will be emailed to participants and posted to a private Facebook group on Sunday mornings beginning the first week of summer break. The private Facebook group serves to promote social support for parents and to provide parents access to additional resources through daily (Monday-Friday) posts (Table 2 contains an example week). The Facebook group will be administered and monitored daily by research staff who assisted in the development of the intervention. The PI ([name]) will meet weekly with the intervention delivery team to ensure the intervention is delivered according to protocol. To ensure the PI remains blinded, no participant identifying information will be used in these meetings.

**Figure 2 figure2:**
[figure not shown]
Intervention framework.

**Table 2 table2:** Example week of Facebook posts.

Day	Themes	Topic	Text of the post
Sunday	Intervention Session	Session 1—Consistent Bedtimes	*Today's the day! Click on the link below to begin Session 1 of the i♥rhythm project. #sleep #consistencyiskey #bedtimeroutine*
Monday	Topic Introduction	Setting Up a Calming Bedtime Routine	*With long days and busy family schedules, how do you set up a calming bedtime routine for your child? Read this resource to learn more (link). If you have any issues accessing the Dropbox folder, please let us know. #sleep #bedtime routine*
Tuesday	General	Reminder About Resources	*Just a quick note that additional resources can be found in our Box folder (link). Over the next few weeks, we will be covering the following topics: Consistent Bedtimes, Light Exposure, Physical Activity, Meal Timing, and Maintenance. Remember to reach out if you have any questions! #resources*
Wednesday	Barriers and Solutions	Helping Your Child Fall Asleep Independently	*Is your child having trouble falling asleep independently? Click on the link to read about strategies to get your child's sleeping schedule back on track. If you have additional strategies to share, feel free to comment with them below!*
Thursday	Status Update	Check-in poll about progress	*What are some strategies that helped your child keep a consistent bedtime this week? For the poll, you can choose multiple options, add your own, or type it in the comments. Note: the results of the poll are not anonymous.*

#### Control

Control participants will not receive an intervention and will only participate in Time 0, 1, 3, and 4 assessments as outlined in Table 1.

### Process Evaluation

Process evaluation documents intervention delivery and provides insight into the mechanisms by which programs work [44]. Following the framework of Baranowski and Jago [45], we will assess recruitment of participants, maintenance of participation, the context of implementation, resources necessary for implementation, implementation (completion of sessions, daily diaries, and engagement in social media), reach, barriers to implementation, and exposure to the program. Participant completion of sessions will be monitored via logins, video views, and completion of interactive content and diary data. Engagement in social media will be collected via manual abstraction from the newsfeed of the private group [46]. Other issues such as acceptability will be assessed by questionnaires after intervention. Postassessment interviews will examine (1) acceptability of the interventions, (2) perceived benefits of participation, (3) barriers to participation, (4) reasons for drop out. Following the intervention (Time 1) and final data assessment (Time 3), qualitative interviews will be conducted. Interviews will use a standardized script, open-ended questions, follow-up questions, prompts, and areas to probe. Interviews will be conducted until theoretical saturation is achieved [47,48]. Thematic data analysis will identify common themes and patterns [49]. Each statement will be assigned a broad category and assessed for meaning units, specific categories, and subcategories. These will be compared and contrasted by gender, overweight status, and SES level.

### Data Collection

Two weeks before the scheduled assessments, actigraphs will be mailed to the child’s home. A link to an online instructional video will demonstrate proper wear and how to avoid covering the accelerometer with clothing [50]. Children will wear actigraphs (GT3X-BT; ActiGraph, LLC) on the wrist of their nondominant hand to assess their sleep and activity for 7 days and 8 nights during the school year. Parents will complete a daily sleep diary and monitor-wear logs to record the times the accelerometer is removed and the reason for removal [51-53]. A paper copy of these forms will also be provided for note-taking purposes. Parents will download an app called Centrepoint (ActiGraph, LLC) to their phone and will be asked to use this app to upload their child’s actigraph data to the cloud via a Bluetooth connection. Download instructions will be emailed to participants and research staff will follow-up to provide a PIN. During this follow-up, the parent will perform a preliminary upload to verify data are transferring. The Centrepoint app will allow research staff to monitor participants’ compliance with accelerometer wear and ensure sufficient wear time is achieved before coming into the sessions. Sufficient wear time will be defined as having at least five nights [51] and days of activity data. Valid days will be defined as at least ten hours of wear time in 24 hours [54]. As sleep will not be scored until after the actigraphs are returned, this determination will be made by research staff using visual inspection of the Centrepoint data. During the 8 days when the monitor is worn, parents will be asked to complete a web-based dietary food recall using the Automated Self-Administered 24-Hour Dietary Assessment Tool (ASA24) 3 times and complete a series of questionnaires (described below). Completion of the ASA24 will be monitored by the research staff. If the online diary status shows as incomplete, the parent is emailed the next day to complete another day of intake until 3 full days are complete. The aim is to obtain dairy intake data for 2 weekdays and 1 weekend day.

Approximately 1-2 days following the eighth day of accelerometer wear, assessment visits will be scheduled. Participants will be scheduled to arrive at the laboratory at least six hours before their typical bedtime. Typical bedtime will be estimated using visual inspection of the actigraphy data in Centrepoint along with parent sleep diaries. On the day of the laboratory visit, participants will be asked to avoid intake of caffeine, chocolate, nonsteroidal anti-inflammatory drugs, and cannabidiol products. Upon arrival at the laboratory, anthropometric assessments will be conducted and actigraph data will be downloaded. Children and their parents will be taken to a dimly lit (<5 lux) circadian phase assessment suite (a private room with a table and chairs and a futon chair with an adjoining bathroom). Following established procedures with children, saliva (~1 mL) samples will be collected using untreated Salivettes (Starstedt, Inc.) every hour beginning 5 hours before and ending 1 hour following typical bedtime. Before the collection of samples, children will be seated for 10 minutes to minimize postural effects on melatonin concentration. If participants eat or drink before the sample collection, they will gently brush their teeth with a soft-bristled toothbrush and water. Saliva samples will be centrifuged and frozen for later analysis of melatonin. Assessment visits will end after the final saliva sample collection.

To compensate participants for travel and the inconveniences associated with assessments requiring a minimum stay of 7 hours in the laboratory and keeping children awake past their bedtime at each assessment, participants will be offered US $100 at Times 0 and 1 and US $150 at Times 2 and 3 to encourage participation in assessments.

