#### Actigraphy

Actigraphs (GT3X-BT) worn on the wrist of the dominant hand 24 hours a day for 7 days will measure sleep duration, the timing of sleep onset, and waking as well as physical activity and light exposure. Using the Sadeh algorithm [62] epochs will be scored as sleep or wake. According to established protocols [17,63], each sleep episode reported in the parent diary will be inspected in the activity data. Nights will be considered valid if the participant provided 20 minutes of wear time before sleep onset. Nonwear time in the hour before bedtime must be less than 60 minutes unless confirmed by the wear log, or unless ambient light data are available to confirm bedtime. Sleep onset will be defined as the beginning of the first 3 consecutive epochs scored as sleep. Sleep offset will be defined as the last 5 consecutive minutes of sleep occurring before 15 minutes after the reported wake-up. Sleep midpoint will be defined as the midpoint between sleep onset and offset. Children’s physical activity will be measured using vector magnitude activity counts captured in 60-second epochs and categorized into sedentary, light, moderate, and vigorous physical activity using established cut points [64].

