### Data Analysis Plan

A statistical analysis plan will be written before the database is locked and breaking the blind. The feasibility of the intervention will be assessed from staff-collected and parent-reported variables according to the previously stated criteria. We will examine the internal consistency of all questionnaires using Cronbach alpha. Decisions regarding the need for changes before further testing of the intervention will be made based on the attainment of feasibility criteria and postassessment interviews. This pilot study is not powered to detect differences in outcome variables and therefore drawing conclusions about the efficacy of the intervention based on statistically insignificant differences in change in BMI, standardized BMI, or circadian phase is inappropriate [30,77-79]. Descriptive statistics and confidence intervals will be used to examine mean differences and the effect sizes of change in outcome variables between conditions. Exploratory analyses will be used to estimate intervention effect over time using a repeated-measures regression approach while controlling for sex and SES, and accounting for the within-subject correlation and the nesting of children within families. The model will include a fixed effect for the repeated measurements (Times 0, 1, 2, and 3), a random subject effect, and treatment group as a between-subjects factor (i♥rhythm and control). Children’s differences across the groups in change in BMI, standardized BMI, and circadian phase will be tested using a group × time interaction. Change in BMI was included as an outcome because it is considered the preferred measure of change in adiposity among children over periods of less than 1 year [80-82]. Separate models will examine other dependent variables of interest including sleep duration, the timing of sleep onset, and interdaily similarity. Because the study is not powered to detect group differences in outcomes, effect sizes will be examined based on the standardized mean difference (Cohen *d*) criteria for small (0.20), medium (0.50), and large (0.80) [83,84].

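### The ten-hour valid-day rule is not limited to waking time on a device worn day and night, so the pre-visit wear check can pass days with little waking activity data

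*Protocol article*

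**What the plan says.** The wear rules are in two sections of the protocol article.

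- **Data Collection, number of days and nights:** "Sufficient wear time will be defined as having at least five nights [51] and days of activity data".
- **Data Collection, what makes a day valid:** "Valid days will be defined as at least ten hours of wear time in 24 hours".
- **Data Collection, how it is judged:** "As sleep will not be scored until after the actigraphs are returned, this determination will be made by research staff using visual inspection". The data are viewed in Centrepoint before the family comes in. Parents also keep a daily sleep diary and a log of when and why the device was removed.
- **Actigraphy, wear schedule:** the device is worn "24 hours a day for 7 days will measure sleep duration", and it also records activity and light.
- **Actigraphy, valid nights:** "Nights will be considered valid if the participant provided 20 minutes of wear time before sleep onset", with further conditions on non-wear in the hour before bedtime.
- **Actigraphy, activity outcome:** it is "measured using vector magnitude activity counts captured in 60-second epochs and categorized into sedentary, light, moderate, and vigorous physical activity".

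Table 1 lists physical activity/inactivity as a secondary outcome at Times 0, 1, 2 and 3. The article gives no other valid-day rule, and neither section confines the ten hours to waking time or takes sleep out before wear is counted.

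**The concern.** On a device worn only in the daytime, ten hours of wear is ten hours of waking data. On a device also worn in bed, hours asleep count toward the same ten. A child who wears it from 8:00 PM to 6:30 AM and leaves it off all day has 10.5 hours of wear and, as the rule is written, a valid day.

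At stake is whether the activity outcome has usable data behind it. Staff use the rule to confirm that wear is sufficient before the visit. A child who passes on overnight wear gives staff no stated reason to ask for more, so the waking data are never collected. With a target of 40 dyads, such losses are hard to absorb. Daytime activity is also one of the intervention's four behavioural topics. The Objective includes testing the assessment procedures and deciding whether measures need modification, so a check that counts overnight wear as activity data could make this measure look more workable than it is.

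**Working it through.** The ten-hour threshold is a definition, so there is no planned figure to reproduce. The check is how much waking wear it guarantees.

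**Inputs**

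- Threshold: 10 h of wear in 24 h (Data Collection).
- Wear schedule: 24 h a day, so sleep counts as wear (Actigraphy).
- Days required: 5 (Data Collection).
- Wear before sleep onset for a valid night: 20 min, or 0.33 h (Actigraphy).
- Sleep duration S: not given for these children aged 5 to 8. Assumed range 8 to 11 h.

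**Formulas**, for a night worn in full

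- Minimum waking wear for a valid day = max(0, 10 − S).
- Share of waking time = minimum waking wear / (24 − S).
- For comparison, if the ten hours had to be waking: share = 10 / (24 − S), and total wear with the night = 10 + S.

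| S (h) | Waking time (h) | Waking wear needed as written (h) | Share of waking time | Share under a 10 h waking rule | Total wear under that rule (h) |
|---|---|---|---|---|---|
| 8 | 16 | 2 | 12.5% | 62.5% | 18 |
| 9 | 15 | 1 | 6.7% | 66.7% | 19 |
| 10 | 14 | 0 | 0% | 71.4% | 20 |
| 11 | 13 | 0 | 0% | 76.9% | 21 |

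**Adding the valid-night rule.** If the night must also be valid, the floor is 0.33 h. This changes only the last two rows: 0.33/14 = 2.4% at S = 10 and 0.33/13 = 2.6% at S = 11.

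**Counting by calendar day.** The result does not depend on where the 24 hours start. Sleep from 21:00 to 07:00 every night puts 7 + 3 = 10 h of wear into each midnight-to-midnight day.

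**Over the required five days.** As written, the minimum is 5 × 0 = 0 h to 5 × 2 = 10 h of waking wear in total. A waking rule would secure 5 × 10 = 50 h. Nothing stops one recorded night from counting toward both the five nights and the five days.

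**The case against.** The strongest defence is that the rule is a compliance check. It sits in the Centrepoint monitoring step, and the article never says that it selects days for the activity outcome. A statistical analysis plan is promised before database lock and may set a waking-wear minimum. Nights and days of activity data are named separately, and unscored sleep is given as the reason for visual inspection, which suggests that staff are meant to tell night wear from day wear. A child who removed the device every morning would probably be noticed on screen or in the wear log. Physical activity is secondary, is not among the dependent variables named in the Data Analysis Plan, and the pilot is not powered for outcomes.

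Much of this stands. Use of the rule at analysis is an inference, although it is the only valid-day rule given. Inspection may catch empty days, but no stated criterion tells staff to reject them. The promised plan does not fully answer the point, because the article states a rule, and that rule acts while data are still being collected.

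Three stronger readings are tempting, and the article does not support them.

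- **Sedentary time contains sleep.** The Actigraphy section scores epochs as sleep or wake and checks each diary-reported sleep episode against the recording. Nothing says that sleep epochs are classed as sedentary.
- **Interdaily similarity is compromised.** The Data Analysis Plan names it ("Separate models will examine other dependent variables of interest including sleep duration, the timing of sleep onset, and interdaily similarity") but gives no derivation or day rule, so nothing ties it to ten-hour days.
- **The between-group comparison is biased.** That would need daytime wear to differ by arm. The documents give no frequency of night-only wear, and no size or direction of bias can be derived.

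**Conclusion.** The point holds as a fault in a stated data-collection rule. As written, the rule guarantees only 0 to 2 hours of waking wear per valid day when the night is fully worn, or 0% to 12.5% of waking time, against 62.5% to 76.9% if the ten hours were waking hours. The range rests on an assumed 8 to 11 hours of sleep. At 8 hours the gap is narrower, but it does not close.

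These are the minimum that the rule allows, not a forecast of how children will wear the device. The consequence is confined to the amount of waking data behind the secondary physical activity/inactivity outcome. Sleep measures have their own night rule, and the feasibility criteria, BMI and DLMO do not depend on this one. Severity is minor to moderate.

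**What to change.** Under Data Collection, define a valid activity day as at least ten hours of waking wear. At the Centrepoint check before the visit, exclude the diary-reported sleep period. At analysis, exclude the scored sleep period. State this rule separately from the valid-night rule under Actigraphy, so that nights and activity days are each judged on their own criterion.

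For data already collected, re-screen the recordings and report how many days fail the waking rule.

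No new measurement is needed, since sleep diaries, wear logs and Centrepoint data are already part of the procedures. The cost is that some days now counted as valid will be dropped, or families will be asked for extra days of wear.

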### Primary Outcomes

#### Feasibility Criteria

The feasibility of the study will be established by our ability to recruit the needed sample size and retain at least 80% of participants at Time 1 and 60% at Time 3. The feasibility of the intervention will be determined based on delivery of all components of the intervention as designed, favorable acceptability ratings by 80% of parents randomized to the experimental condition, completion of greater than 60% of daily self-monitoring, and views of 80% of intervention sessions by the experimental sample.

#### Treatment Acceptability

Participants assigned to the experimental condition will complete the Treatment Acceptability Report Form-Revised (TARF-R) at Time 1. The TARF-R is a 20-item global measure of treatment acceptability for behavioral interventions. Examples of items include (1) “How clear is your understanding of this intervention?”; (2) “How acceptable do you find the intervention to be for you and your child?”; (3) “How reasonable do you find the intervention to be?”; (4) “How likely is the intervention to make improvements in your child’s health habits?”. The TARF-R has demonstrated good internal consistency (αs>.69) and evidence of construct validity (reference). A favorable rating is considered 4 or greater.

#### Anthropometrics

While feasibility criteria will serve as a primary outcome for this study, change in BMI will serve as the primary outcome for the fully powered randomized controlled trial. BMI is the most common indicator of body size and has been consistently correlated with metabolic problems in children. Participants’ height and weight will be measured. Weights will be assessed in light clothing without footwear using a Healthometer digital scale. BMI (kg/m^2^) will be computed and BMI percentile and standardized BMI will be calculated from age and gender normative data. BMI percentile will determine the weight status group. Based on baseline BMI percentiles, children will be classified into 3 weight categories: healthy weight (5th percentile to <85th percentile for BMI), overweight (≥85th to <95th percentile for BMI), and obese (≥95th percentile for BMI). Change in BMI and standardized BMI are the best proxy measures for change in fat mass and standardized fat mass, respectively, and will assess exploratory hypotheses.

